**Data collection tool**

A criteria based audit will allow us to compare current practice to the local standards. This involves structurally observing intrapartum care and determining the adherence to the local PartoMa guidelines. Therefore, a data collection is created, based upon the PartoMa guidelines and additional information on the labouring women to categorize the labours and to systematically note the observations and key events during each shift and labour is included.

**Data collection:** The gestational age (GA) will be calculated based on the available information: using the last menstrual period (LMP), ultrasound (US) findings from first trimester, fundal height measured in the first trimester or fundal height recorded on admission. This information will be collected after delivery. Please refer to supplement 1 for further details on data collected during clinical observation.

**Recordkeeping:** For now, I will solely prepare for the validation study, but photocopying the file and systematically saving it**.** Each file will have a number assigned to it and names will be covered. The timing of the recordkeeping will depend on the mode of delivery due to the loss of records at the MMH. A vaginal delivery can be recorded immediately after delivery and a CS after the morning meeting the next day latest. Method to collect data: KoBoToolbox.

**Data analysis**

PartoMa guidelines will be used to assess whether FCM was done according to the standards set of criteria we have assessed. The relevant criteria are described in the PartoMa guidelines. The influence of the following factors on adherence will be assessed: low-vs high-risk pregnancies, experienced vs non-experienced (self-identified), midwives or doctors, nulli- vs multipara, morning vs afternoon vs night shifts, occurrence of key vs non key events will be calculated:

1. Participant characteristics will be descriptively presented using means and standard deviations for continuous variables and frequencies and percentages for categorical variables.
2. FHM adherence according to standard will be calculated:
   - Percentage of number of labours that completely adhered to guidelines (dichotomized outcome, yes/no) for the following 3 groups: heart rate monitoring, contraction monitoring and both.
   - Score of FHM adherence, defined as: (number of observations) / (number of expected observations given the duration of labour).
   - Score of contraction monitoring adherence, defined as: (number of observations) / (number of expected observations given the duration of labour).
   - Score of maternal pulse adherence, defined as: (number of observations) / (number of expected observations given the duration of labour
   - Average interval between observations: average in minutes and standard deviation
3. Influence of low-vs high-risk pregnancies, experienced vs non-experienced midwives or doctors, nulli- vs multipara, morning vs afternoon vs night shifts, occurrence of key vs non key events on the FHM score will be assessed, using a Poisson distribution analysis.
4. Descriptive analysis of structural challenges and woman-to-staff contact.

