**Selection of labours**

Observations will be held at the maternity ward of MMH. At least 150 labours will be observed, maximum 8 labours per one shift. This corresponds to the shifts of the midwifes: morning shift: 7.30 am till 2.30pm, afternoon shift: from 2.30 pm till 8.30 pm and night shift: 8.30 pm till 7.30 am. Even though a labour exceeds the shift, observations will be continued until delivery. A schedule of which shift to incorporate will be created in advance in order to shadow as many midwives as possible, with different levels of experience. Labours will be selected based on the following criteria: the first women to reach active phase who meets the inclusion criteria and is either being admitted or already at the ward. The inclusion of labours will be both high- and low-risk (as determined antenatally or on admission), both nulli- and multipara. High-risk pregnancies are defined as women with a previous caesarean section, induced labour by oxytocin or having pregnancy, medical complications (preterm and postterm labours, PROM, meconium, maternal illness, severe bleeding, foetal distress (Intrauterine foetal death, IUFD), poor progress (crossed alert line of the partogram), severe hypertensive disorder, fever or other infections). Key events are defined as: maternal bleeding, temperature measurement (fever), fits, bleeding, caesarean section (CS), intra-uterine resuscitation, fluids etc. A labour will be observed once the woman reaches active phase of labour (4 cm cervical dilatation) until complete delivery of the baby (independent on whether the cervical dilatation is reached at admission or during intra-facility care). In case of an IUFD detected during labour, observations will be stopped, but data will be included in the results. Exclusion criteria for labour**:** woman for elective CS, diagnosed with IUD by staff before admission by ultrasound (US) or women who are send for immediate CS upon arrival. An information sheet in Kiswahili and a verbal explanation by a midwife in Kiswahili will be provided to the labouring women on the aim of this study: observing staff taking care of her. Informed consent will be asked from the labouring women (on arrival) and from the staff as a group (once study commences one time). Staff can tell upfront in case they do not want to participate. As an observer, my job is to observe the intrapartum care and I am not expected to intervene.

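### The adherence scores are uncapped count ratios that ignore when checks were made, so a score of 1.0 does not show guideline-adherent timing; the yes/no percentage also depends on labour duration

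*Protocol*

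**What the plan says.** The Data analysis section, item 2, lists several adherence measures. Three are scores with one common form. For the foetal heart rate the entry reads "Score of FHM adherence, defined as: (number of observations) / (number of expected observations given the duration of labour". The entry for contractions has the same structure: "Score of contraction monitoring adherence, defined as: (number of observations) / (number of expected observations given the duration of labour". The maternal pulse is treated likewise: "Score of maternal pulse adherence, defined as: (number of observations) / (number of expected observations given the duration of labour". Beside these scores stand a per-labour outcome, "Percentage of number of labours that completely adhered to guidelines (dichotomized outcome, yes/no", given for heart rate monitoring, contraction monitoring and both together, and a spacing statistic, "Average interval between observations: average in minutes and standard deviation".

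Item 3 takes one of these forward. It names risk group, staff experience, parity, shift and key events as factors, whose influence "on the FHM score will be assessed, using a Poisson distribution analysis".

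The number of expected checks depends on the observation window. Under Selection of labours, "A labour will be observed once the woman reaches active phase of labour (4 cm cervical dilatation) until complete delivery of the baby", so the window differs from labour to labour. The checking intervals themselves are not in the protocol: "The relevant criteria are described in the PartoMa guidelines".

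**The concern.** A guideline that sets a checking interval is met when no stretch of labour longer than that interval passes without a check. A total count divided by an expected count does not measure this. Ten checks after an alarm count the same as ten checks spread over the labour. Because nothing caps the ratio at 1, a heavily checked labour also raises the group mean and can hide a neglected one.

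The audit exists to describe adherence, and item 3 asks which factors influence it. If, for example, extra checks cluster around key events, labours with such events would score higher even where earlier hours went unmonitored.

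The yes/no outcome does respond to timing if it means that every due check was made on time. It then becomes harder to achieve the more checks are due. A comparison of this percentage between groups would be confounded if the groups' labours differ in length.

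**Working it through.** The protocol gives no adherence figure to reproduce. The inputs from the protocol are the ratio definition, the yes/no outcome, the mean and SD of the interval, and the window from 4 cm to delivery. The checking interval, labour durations and adherence per check are not given. The values below are assumptions for illustration.

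**1. Blindness to spacing.** Assume a 6-hour (360-minute) labour and a 30-minute interval. Expected checks = 360 / 30 = 12.

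| Pattern | Score | Longest gap | 30-min intervals with a check |
|---|---|---|---|
| 12 checks, every 30 min | 12/12 = 1.00 | 30 min | 12 of 12 |
| 12 checks, every 5 min in the first hour, then none | 12/12 = 1.00 | 360 − 60 = 300 min | 2 of 12 (0.17) |
| 18 checks, every 5 min in the first 90 min, then none | 18/12 = 1.50 | 360 − 90 = 270 min | 3 of 12 |

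**2. Offsetting between labours.** The third labour (1.50) and an equally long labour with 6 of 12 checks (0.50) average (1.50 + 0.50)/2 = 1.00.

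**3. Whether the interval statistic reveals the gap.** For the second pattern:
- Counting the last gap to delivery, there are twelve gaps of 5 min and one of 300 min. Mean = 360/13 = 27.7 min, SD = 81.8 min. The mean looks acceptable; only the SD shows the problem.
- Without the last gap, mean = 5 min and SD = 0. Five unmonitored hours disappear.

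The protocol does not say which applies, or whether the statistic is per labour or pooled.

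**4. The yes/no outcome and duration.** If each of n required checks is made with probability p, independently, P(complete adherence) = p^n. With a 30-minute interval, labours of 2, 4 and 8 h require n = 4, 8 and 16.

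| p | n = 4 | n = 8 | n = 16 |
|---|---|---|---|
| 0.80 | 41% | 17% | 3% |
| 0.90 | 66% | 43% | 19% |
| 0.95 | 81% | 66% | 44% |
| 0.99 | 96% | 92% | 85% |

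With a 240-minute interval the same labours require 1, 1 and 2 checks, and p = 0.90 gives 90%, 90% and 81%. The direction is the same, but the effect is much smaller.

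**5. A timing-based score on the same examples.** Take the share of labour time during which the last check (or the start at 4 cm, before any check) was no more than 30 minutes ago.
- Evenly spaced: 360/360 = 1.00.
- Bunched in the first hour: minutes 0 to 90 are covered, 90/360 = 0.25.
- Checks at 29, 61, 89 and 121 min: the gaps are 29, 32, 28 and 32 min, so 2 + 2 = 4 of 121 minutes are uncovered and the score is 117/121 = 0.97. Counting fixed 30-minute windows instead would credit only 2 of the first 4 windows for this near-perfect pattern.

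**The case against.** The measures should be read together. A bunched labour with a five-hour gap would count as a failure on the yes/no outcome, if that outcome requires timely checks, and the interval SD may expose it. The protocol never says that a score of 1.0 means adherent care. An observed count over an expected count is also the natural quantity for a Poisson model with an offset, where values above 1 are legitimate. Scoring detail may sit in the statistical analysis plan or in supplement 1, which are not shown.

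Part of this stands. The count ratio is a valid monitoring rate and need not be dropped. The safeguards are only partial, however: the interval statistic can hide the last gap (step 3), and neither it nor the yes/no outcome is named for item 3. The ratio is fixed in the protocol itself and is labelled a score of adherence.

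Three stronger readings are tempting and are not supported.
- A reader might infer that the yes/no outcome mainly measures how short the labour was. A simulation of 200,000 labours (assumed lognormal duration, median 5 h, log-SD 0.6; adherence per check varying between labours) compared how well short duration and true quality of care predict complete adherence. With a 30-minute interval and mean adherence 0.8, the areas under the curve were 0.77 for duration and 0.68 for quality when quality varied little (SD 0.07), but 0.68 and 0.83 when it varied more (SD 0.15). With a 240-minute interval, quality predicted better in every case tried (0.62–0.81 against 0.59–0.60).
- A reader might infer that parity or risk groups will differ on the yes/no outcome. The protocol gives no durations by group, and item 3 names the FHM score, not this outcome.
- A reader might attach one coverage figure to a score. If checks fall at random, a score of 1.0 means 1 − e^(−1) = 63% of intervals covered. Regular checks would give 100% and the bunched example gives 17%. How often bunching will occur is unknown.

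**Conclusion.** The point holds for the scores from the text alone. All three are uncapped and blind to spacing, so a score of 1.0 is compatible with anything from perfect timing to a 300-minute gap in the 6-hour example, and item 3 inherits this through the FHM score. That example assumes a 30-minute interval; the property itself holds for any interval.

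For the yes/no percentage, the narrower statement holds: for the same care per check it falls as more checks come due, and comparisons of it are confounded if durations differ. The size depends on the interval, the adherence level and independence between checks, none of which the protocol gives. The change is worth making, but the planned measures are not worthless without it.

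**What to change.** - Add a timing-based score for each of the three kinds of check: the share of observed labour time, from 4 cm to delivery and counting the first and last gaps, during which the last check was within the guideline interval for that phase. State a small tolerance in advance. The score lies between 0 and 1. Report it beside the count ratio, as the measure of adherence.
- Keep the count ratio, described as a monitoring rate, for the Poisson model in item 3, with the observed count as outcome and the expected count as offset. Repeat item 3 on the timing-based score with a model suited to a proportion; the Poisson count model does not carry over to it unchanged.
- Show the yes/no percentage by labour duration.

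No extra data should be needed, because the planned interval statistic already requires the time of each check. The costs are somewhat more programming, a second model for item 3, and reported adherence that will probably look less favourable.
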